# Introduction, Principles and Rationale

Cerebral palsy is a syndrome in which the body is abnormal in posture and movement, which is caused by a static brain pathology during the growth and development of the brain. Cerebral palsy is commonly found in developed countries with the incidence of 7 per 1000 livebirths.^1^

The causes of cerebral palsy can occur during pregnancy, such as high blood pressure, infection, exposure to toxic substances, heart and respiratory diseases, as well as metabolic diseases. Perinatal causes are placenta previa, prolonged labor, umbilical cord prolapse, abnormal fetal presentation, cephalopelvic disproportion, and preterm delivery. And postpartum period cases are such as head injury, brain vessel disorders, illnesses that cause cerebral ischemia or oxygen.^2,^ ^3^

The classification of cerebral palsy is determined according to neuromuscular disorders and the distribution of disorders includes the spasticity (spastic type), the group with low muscle tension (hypotonic type), abnormal movement (dyskinetic type), stiffness (rigidity), balance disorder (ataxic type), and mixed disorder (mixed type).^4^ Other associated disorders such as seizures, mental retardation, eye and vision disorders, language and communication problems, hearing problems, and swallowing problems can also be found. Therefore, treatment requires the cooperation and coordination of the pediatric team, rehabilitation medicine, orthopedic surgeons, physical therapists, occupational therapists, therapists and psychologists to determine the appropriate treatment.

The spasticity type is the most common type of cerebral palsy^1^ that commonly affects gait from a low level, such as a decrease in walking speed or slight balance disorders, to a high level, such as having to use a wheelchair to move around all the time, and not being able to control the head or body to resist gravity. Treatment of this type of disorder ranges from the use of medications such as antispasmodic drugs, intramuscular injections, botulinum A toxin, intraspinal injections, and non-pharmacologic treatment such as physical therapy, splinting, and surgery.^5^ If the patient has mild symptoms, every patient should undergo physical therapy to make the muscles flexible without spasticity that will greatly affect the patient's walking, especially the hip muscles, thigh muscles, and leg muscles, as well as the upper limb muscles.^6^

However, because other provincial hospitals from the provincial to community level hospitals, the workload of the physiotherapy group is quite large, and Thailand has Thai traditional medicine as an alternative to treat various diseases. With reports that Thai massage can actually reduce muscle spasm in patients with cerebral ischemia, allowing patients to use the affected arm or leg well, and towards a better quality of life. In addition, Thai massage can also reduce stress and anxiety. Therefore, the application of traditional Thai massage to reduce muscle spasms to increase the efficiency of walking is another option that should be emphasized to reduce the burden on the physiotherapy group and increase the opportunity to access services for patients in areas where there are not enough physiotherapists.^8^

Nowadays, massage is increasingly used to treat diseases in medicine to reduce muscle spasms, such as

muscle spasms due to cerebral embolism (post stroke spasticity)^7^, multiple sclerosis^9^, cerebral palsy, etc. Most of them were found to be effective or equivalent to standard treatment.

Massage not only relaxes the patient, studies have shown that massage also has many benefits, such as helping to stretch stiff muscles, keeping muscle fibers elastic at the right level, breaking down the fascia that binds to the muscles, stimulating the circulatory system and the nervous supplied muscles to work better, etc.^7^ However, studies have shown that a small percentage of people who undergo massage experience side effects later, such as soreness, physical fatigue, headache, bruising, etc.

The effects of different types of massage, such as Swedish, Deep cross friction, Pakistani and Thai massage, on muscle stiffness in people with cerebral palsy compared to normal physical therapy.^11-15^ Table 1 showed that muscle stiffness is measured in the form of the Modified Ashworth Scale (MAS), abnormal reflex or Gross Motor Function Measure 88 (GMFM-88). It can be seen from past studies that there is still no There is a clear conclusion as to whether massage can actually reduce muscle spasms in patients with cerebral palsy, which may be due to a number of factors, such as the insufficient number of people participating in the study. The duration of the trial was not consistent with the treatment model. The format of the experiment was not a randomized controlled trial. Absence Concealment There is systematic bias, etc. (Table 2).

**Table 1** Massage Patterns and Duration ^11-15^

[figure not shown]

**Table 2** Research methodology and results of massage ^11-15^

[figure not shown]

Reducing gait disorders caused by muscle spasm is another goal of treating the disease. Therefore, measuring the effect of massage on walking using a 3D gait analysis is another effective method. Because a large amount of quantitative data is collected during the test to increase the accuracy of analysis and evaluation of gait performance and reduce systematic error by displaying various forms of results such as temporal spatial, kinetics, kinematics, electromyography data, etc.^16^

This is because gait analyzers can provide large amounts of data, and they are quite complex. At present, representatives of such datasets have been invented for easy communication, such as the Gillette Gait Index (GGI), Gait Deviation Index (GDI), Gait Profile Score (GPS), etc^17^. The study found GPS represents the most useful dataset because no large reference dataset is required. GPS is calculated from 9 sets of Gait Variable Scores (GVS) combined to provide an overview of all walks. While GVS represents kinematics data comprises 9 sets of Pelvic tilt, Hip flexion/ extension, Knee flexion/ extension, Ankle dorsiflexion/ plantar flexion, Pelvic obliquity, Hip abduction / adduction, Pelvic rotation, Hip internal/ external rotation and Foot progression angle. GVS is calculated as the square root of the mean of the difference between the walker's kinematics data and the person's normal value (Averaged Normative Reference Dataset) squared, also known as Root Mean Square Error (RMSE). Therefore, the factors that affect GPS includes pelvic tilt and rotation, ability to flex/extend/rotate/adduct/abduct the hips, ability to flex/extend the knee, ability to dorsiflex/plantarflex the ankle. The higher GPS, the more gait abnomality.^17^

If there is precise processing, create a good research protocol to clearly define the duration of the experiment and the sample, it will lead to a very accurate description of the effect of massage on muscle tension that affects the gait of patients with cerebral palsy. Although the results did not differ between massage and physical therapy. If there were significant differences within the intervention group, Thai massage may also be another non-surgical treatment option and is considered to support Thai wisdom in the treatment of diseases.

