# Objectives of the research project

To study and compare the effects of traditional Thai massage with regular physical therapy. In the development of gait in patients with spasticity, it was evaluated from the gait profile score.

- Primary outcome: Gait profile score (GPS)
- Secondary outcome: Modified Ashworth Scale, Temporal spatial data, Kinetics data, Oxygen consumption, Electromyography and Pedobarography

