# Research Methods and Research Patterns Research Schedule

Research Model: Crossover randomized controlled trial

- Patients who meet the criteria and agree to participate in the research will be interviewed and examined to collect basic information and make an appointment for gait analysis.

- Participants will be analyzed by motion capture machine from Motion analysis corporation, Santa Rosa, CA, USA and recorded using Cortex 6.2 program. Data will be analyzed using Orthotrak and participants will be randomly assigned to group A and B.

- Participants will be taught home program physical therapy and will be taught from the beginning of the study to the end of the study for 18 weeks.

- Group A will receive traditional Thai massage according to the regulations mentioned above for 6 weeks, and then will be analyzed for a second time.

- Group B will receive regular physical therapy for 6 weeks, then will undergo a second walking analysis.

- Once Group A or B has undergone a second gait analysis, a 6-week interval will be given.

- Once the third gait analysis is undertaken, treatment will be alternated where group A will receive physical therapy as usual. Group B will receive a traditional Thai massage for 6 weeks.

- Both groups will then be analyzed for a fourth time.

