# Home Program Physical Therapy

Participants or their parents will be taught physical therapy at home by doing it 5 times/week for at least 30 minutes each time, for a total of 150 minutes/week. The patient performs shoulder abduction/flexion, elbow flexion/extension, hip extension/abduction, and knee extension/flexion in repetitive movements for 3-5 minutes on both sides, and ambulatory training is the practice of moving both arms and legs forward, backward, left and right (side-to-side). Gait aid is allowed if available.

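### The rationale would read a significant before-after change in the massage group as support for massage even when massage and physical therapy do not differ; that inference is unsound and should be removed

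*Protocol*

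**What the plan says.** The last paragraph of the protocol's Introduction, Principles and Rationale contains two linked statements. The first is "Although the results did not differ between massage and physical therapy"; the second follows directly: "If there were significant differences within the intervention group, Thai massage may also be another non-surgical treatment option". The same sentence adds that this would count in favour of Thai traditional knowledge.

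The operative sections are comparative throughout. The objective is "To study and compare the effects of traditional Thai massage with regular physical therapy", judged on GPS. The design is given as "Research Model: Crossover randomized controlled trial". The sample size is for a difference between two means, 13.90 against 11.12.

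On background treatment, the methods section says of home physical therapy that participants "will be taught from the beginning of the study to the end of the study for 18 weeks". The Home Program section sets the amount, "for a total of 150 minutes/week", and the Washout Period section says that it continues unchanged through washout. Massage itself is two 30-minute sessions a week, or 60 minutes. Gait is analysed four times: before and after each six-week treatment period.

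**The concern.** A before-after change in one treatment period is not a randomised comparison. It collects everything that happened over those six weeks. Here that includes a concurrent exercise programme with more weekly minutes than massage, familiarity with the gait laboratory, time and growth, and regression to the mean. In group A the massage period also coincides with the first six weeks of the home programme, so any start-up benefit of that programme falls entirely within the massage change.

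No randomised period has the home programme alone, a sham, or nothing. If the randomised comparison were null, the sentence would still invite a favourable conclusion about massage from evidence that cannot separate massage from what accompanied it. The same introduction criticises earlier massage studies for not being randomised controlled trials; a before-after reading brings that weakness back.

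**Working it through.** **1. The plan's own figure.** Inputs from the sample-size section: means 13.90 and 11.12 (difference 2.78), SDs 4.9 and 1.3, alpha 0.05 (taken as two-sided), power 0.80.

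n per group = (4.9² + 1.3²)(1.960 + 0.842)² / 2.78² = 25.70 × 7.849 / 7.728 = 26.1.

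The stated 26 per group is reproduced (27 if rounded up), and 26 × 1.2 = 31.2 gives the stated 32. These figures size a between-treatment difference. In a crossover everyone has a massage period, so 2 × 32 = 64 or 2 × 26 = 52 participants would contribute a massage before-after change.

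**2. How often the within-massage test is significant when massage does nothing.** The protocol gives no SD of change, correlation or expected background change. Assumptions: SD 4.9 before and after, within-patient correlation r of 0.5 to 0.9, and a GPS improvement of 0.5 or 1.0 degree from causes other than massage.

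- SD of change = 4.9 × √(2(1 − r)) = 4.90, 3.10 and 2.19 for r = 0.5, 0.8 and 0.9.
- Standard error = SD of change / √N.
- Noncentrality = background change / standard error.
- Probability of significance comes from the noncentral t distribution with N − 1 degrees of freedom, two-sided 0.05.

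| N | r | Standard error | 0.5-degree change: noncentrality, probability | 1.0-degree change: noncentrality, probability |
|---|---|---|---|---|
| 64 | 0.5 | 0.613 | 0.82, 13% | 1.63, 36% |
| 64 | 0.8 | 0.387 | 1.29, 25% | 2.58, 72% |
| 64 | 0.9 | 0.274 | 1.83, 44% | 3.65, 95% |
| 52 | 0.5 | 0.680 | 0.74, 11% | 1.47, 30% |
| 52 | 0.8 | 0.430 | 1.16, 21% | 2.33, 63% |
| 52 | 0.9 | 0.304 | 1.65, 36.5% | 3.29, 90% |

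With no background change the figure is 5%. The 1.0-degree change is 1.0 / 2.78 = 36% of the planned difference.

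The protocol's other SD, 1.3 for the experimental group, does not alter the picture. With 4.9 before and 1.3 after, the SD of change is √(25.70 − 2r × 4.9 × 1.3), which is 4.40 at r = 0.5 and 3.77 at r = 0.9. Both lie inside the range tabulated (2.19 to 4.90).

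**3. The randomised comparison under the same conditions.** Crossovers were simulated (20,000 replicates) in which both treatment periods share the same background change and massage adds nothing. The paired massage-versus-physical-therapy test stayed at about 5% for SDs of change of 2 and 3 and for N of 52 and 64. With N = 64 and a 1.0-degree background change, the full pattern of significance within massage and none between treatments occurred in 72% of trials at SD 3 and 94% at SD 2.

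**4. What a non-significant difference leaves open.** Take 52 completers and r = 0.5. If post-treatment scores alone are contrasted, the 95% half-width is 2.008 × 4.9 / √52 = 1.36. If changes from each period's baseline are contrasted, the SD is multiplied by √2 (equal correlations assumed) and the half-width is 1.93. An estimate just short of significance has an interval reaching about twice the half-width: 2.7 or 3.9 degrees, against the planned 2.78.

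**The case against.** The strongest reply is that this sentence governs nothing. It closes a background section, is hedged, and appears in none of the objectives, methods or sample size, all of which are comparative. The English is a damaged translation: the clause about no difference is a past-tense fragment, and joining it to the next sentence takes some reading. The size of the problem depends on a background change and a correlation that the protocol does not give; at 0.5 degree and r = 0.5 the rate is only 11% to 13%. No GPS threshold applies at entry, which limits regression to the mean. The design also has a home-programme-only stretch, the washout, with gait analyses at both ends.

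Most of this stands and limits the point. A reader might infer that the protocol sets a second formal route to success, or sets the randomisation aside. It does not: there is no such criterion, and the primary test keeps its error rate.

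A reader might also infer that the protocol claims massage is equivalent to physical therapy. The introduction says only that massage "is another option that should be emphasized to reduce the burden on the physiotherapy group" and would widen access where physiotherapists are few. Being an option is a weaker claim than being as good.

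The washout does not rescue the inference. It is not randomised, it follows active treatment, and the rationale does not use it as a comparator. The fragment is most naturally read as a condition on the sentence after it; no other reading of the pair fits as well.

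**Conclusion.** The point holds as a flaw in pre-stated interpretation and should be fixed. The primary randomised comparison is unaffected. What is unsound is reading a significant change within massage as support for massage when the comparison with physical therapy is null.

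The numbers in the table are illustrations: they rest on the assumed background change, the assumed correlation and the SD of 4.9. They show that a modest improvement from other causes can be enough to trigger the favourable reading, not that such an improvement will occur. The qualitative conclusion needs none of them, because the before-after change and the home programme are confounded by design.

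**What to change.** - Delete the within-group fallback from the rationale.
- State instead that conclusions about massage rest on the randomised within-patient massage-minus-physical-therapy difference in GPS, with its 95% confidence interval.
- Label before-after changes within either treatment as descriptive.
- Add that a non-significant difference will not be described as equivalence.

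Optionally, if the investigators want to say that massage can replace physical therapy, they would need a margin in GPS degrees, justified before results are seen, and a check that the planned number supports it. That check depends on whether post-treatment scores or changes from period baseline are contrasted (half-width 1.36 or 1.93 in step 4). This would be an added aim, not a correction.

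The required changes are wording only, with no extra participants or visits. The downside is that the trial loses an easy positive claim if the comparison is null.

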# Objectives of the research project

To study and compare the effects of traditional Thai massage with regular physical therapy. In the development of gait in patients with spasticity, it was evaluated from the gait profile score.

- Primary outcome: Gait profile score (GPS)
- Secondary outcome: Modified Ashworth Scale, Temporal spatial data, Kinetics data, Oxygen consumption, Electromyography and Pedobarography

# Research Methods and Research Patterns Research Schedule

Research Model: Crossover randomized controlled trial

- Patients who meet the criteria and agree to participate in the research will be interviewed and examined to collect basic information and make an appointment for gait analysis.

- Participants will be analyzed by motion capture machine from Motion analysis corporation, Santa Rosa, CA, USA and recorded using Cortex 6.2 program. Data will be analyzed using Orthotrak and participants will be randomly assigned to group A and B.

- Participants will be taught home program physical therapy and will be taught from the beginning of the study to the end of the study for 18 weeks.

- Group A will receive traditional Thai massage according to the regulations mentioned above for 6 weeks, and then will be analyzed for a second time.

- Group B will receive regular physical therapy for 6 weeks, then will undergo a second walking analysis.

- Once Group A or B has undergone a second gait analysis, a 6-week interval will be given.

- Once the third gait analysis is undertaken, treatment will be alternated where group A will receive physical therapy as usual. Group B will receive a traditional Thai massage for 6 weeks.

- Both groups will then be analyzed for a fourth time.

- If the research participant is unable to come to Ramathibodi Hospital for physical therapy or Thai traditional massage every week because they live in a different province or are worried about the situation of communicable diseases such as COVID-19, etc., the research participant can use the treatment plan of the research conducted at Ramathibodi Hospital at the nearest hospital or can do it at home in order to facilitate the research participants in the current situation and prevent loss to follow-up treatment in the future (loss to follow-up) because it is a time-consuming research. The research team will teach the steps of physical therapy and Thai massage to the caregivers of the participants in detail. Video demonstration details of massage methods, and written procedures are created to ensure that caregivers are confident to do it by themself at home. In addition, the researcher will contact the participants every week to inquire problems found, verify accuracy and confirm that they have actually done it (Telemedicine). Moreover, there was research by Paul M Robinson et al.^22^ has compared physical therapy by a professional with physical therapy at home in patients with frozen shoulder after injecting water into the shoulder joint to destroy the fibrosis (hydrodilatation). It was found that the Oxford Shoulder Score (OSS) and EQ-5D were not significantly different.

[figure not shown]

**Figure 3** Research Execution Chart

# Traditional Thai Massage

Two applied Thai medicine therapists with at least 3 years of experience (with a Thai traditional medical license) will provide the treatment, and undergo a diagnostic examination to assess both physical and emotional conditions before starting treatment. Massage is used by placing the thumb on the desired position and press the massage by adjusting the size and direction of the force applied to the weight. Appropriate according to the severity of the disease and age, it may be considered to stretch and relax the muscles with the paws according to the symptoms of the disease, softly, so that the recipient feels the most comfortable and will not press in a way that crushes, rub, or twists the muscles.

The basic massage will take about 10 seconds at each point, while the signal point massage will take about 30 seconds at each point, and the treatment will be placed in a supine, lateral decubitus, and sitting position as appropriate.

Traditional Thai Medicine Massage therapists will perform treatment according to the prescribed standards and procedures. The procedures for traditional Thai massage are adjusted according to participants, and Traditional Thai massage regulations for safety. Developing academic standard guidelines for massage have a total of 10 steps.

| \| 1. Massage the basic line of the legs, starting from the calves up to the thighs, and then back to the calves again. Then press the signal point on the front ankle and then press open the air door in the groin. \| 5 min \| \| --- \| --- \| \| 2. Massage the basic line of the back along the muscles from L5 to C7 level. \| 5 min \| \| 3. Massage the signal points of the outer legs, starting from the hip area, chasing along the thigh to the upper calf. Outer astragalus \| 5 min \| \| 4. Massage the signal points of the inner legs, starting from the thighs to the inner calves. \| 5 min \| \| 5. Massage the basic line of the inner arm, starting from the center of the inner upper arm to the front wrist. \| 2 min \| \| 6. Massage the basic line of the outer arm starting from the center of the outer upper arm to the center of the outer forearm. \| 2 min \| \| 7. Massage the basic shoulder line starting from the upper edge of the outer shoulder blade to the muscles around the nape of the neck, level C7. \| 2 min \| \| 8. Massage the basic line of the neck curve, starting from the nape of the neck, level C7, and chasing along the neck shaft to the base of the skull. \| 1 min \| \| 9. Massage signal points 1, 2 and 5 on the back of the head. At the base of the skull and massage the nerve point in the center of the crown. \| 2 min \| \| 10. Massage the 5 signal points in front of the head above the chin and above the lips, upper lip. \| 1 min \| |
| --- | --- | --- | --- | --- | --- | --- | --- | --- | --- | --- | --- | --- | --- | --- | --- | --- | --- | --- | --- | --- |

The massage will be carried out according to the aforementioned system for 2 days a week. 30 minutes

at a time for 6 consecutive weeks.

